### Eligibility criteria

Participants who, as of March 2026, are enrolled in the MONSTAR-SCREEN-3 study have not withdrawn consent, and have not declined the secondary use of their clinical data or biospecimens (1). Participants in the MONSTAR-SCREEN-3 study must be 18 years of age or older (2). Individuals who participated between May 2013 and September 2025 in either the ToMMo Three-Generation Cohort Study or the Community-Based Cohort Study, who have not withdrawn consent, and have not refused the secondary use of their data or samples will also be eligible. For participants undergoing additional blood collection for clinical performance testing, written informed consent for this study will be voluntarily obtained (3). ToMMo participants must have no history of malignant tumors (4) and must be between 20 and 75 years of age at the time of consent (5). To ensure background comparability, the age and sex distributions of ToMMo participants will be strictly adjusted to match those of patients with solid tumors enrolled in the previous MONSTAR-SCREEN-2 study (UMIN000043899).

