## Methods/design

### Study design

This study was conducted utilizing two platforms in Japan: MONSTAR-SCREEN-3 and the ToMMo. These cohorts provide extensive clinical and multi-omics resources that enable analyses for the development of high-performance MCED and MRD assays.

MONSTAR-SCREEN-3 (UMIN000053975), launched in 2024, is a nationwide multi-center project comprising three cohorts (advanced solid tumors, curatively resectable solid tumors, and hematologic malignancies) enrolling approximately 3,200 patients. Through multi-layered omics analyses, including whole-genome sequencing (WGS), whole-transcriptome sequencing (WTS), proteomics, metabolomics, spatial transcriptomics, and microbiome profiling, molecular and clinical imaging data are integrated to develop next-generation AI-based biomarkers.

ToMMo, established in 2012, is one of Japan’s largest biobank and population cohort research initiatives, originally found to support medical reconstruction following the Great East Japan Earthquake and to advance precision medicine. The project has enrolled approximately 150,000 population-based participants, systematically collecting a wide range of biospecimens (blood, urine, saliva, breast milk, and peripheral blood mononuclear cells) and integrating these materials into comprehensive genomic and omics databases for future medical innovation.

Using existing retrospective clinical and multi-omics data, we will develop AI classifiers for cancer detection and tissue-of-origin prediction based on data from cancer patients in the MONSTAR-SCREEN-3 study and cancer-naïve individuals in the ToMMo cohort. These classifiers will guide the development of MCED and MRD assays, whose clinical performance will then be validated using archived specimens from the MONSTAR-SCREEN-3 study and prospectively collected samples from the ToMMo cohort (Fig. 2).

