## Study population

### Development of AI classifiers for cancer detection and cancer-of-origin prediction

This study will first develop artificial intelligence (AI) classifiers to predict the presence of cancer and identify the tissue of origin using multi-omics data obtained from the MONSTAR-SCREEN-3 study and the ToMMo cohort. In total, multi-omics data from approximately 1,000 consecutive cancer patients (MONSTAR-SCREEN-3) and 1,000 background-aligned cancer-naïve individuals (ToMMo) across about 15 cancer types will be analyzed. Up to 1,000 multi-omics datasets from the MONSTAR-SCREEN-3 study, including tumor WGS/WES, WTS, germline WGS, plasma proteome/metabolome, and oral/gut microbiome data, will be analyzed alongside approximately 1,000 background-matched cancer-naïve individuals from the ToMMo cohort undergoing comparable profiling. Clinical information such as age and sex will be retrieved from the ToMMo database. Plasma proteomic analysis will be performed on approximately 1,000 archived plasma samples from the ToMMo biobank using the O-link HT system. All analyses will be conducted with approval from the ToMMo Sample and Data Access Committee. The datasets obtained from both the MONSTAR-SCREEN-3 study and the ToMMo cohort will be integrated to develop deep learning-based AI classifiers, including the Cancer Signal Classifier (detecting the presence of cancer) and the Cancer Signal Origin Classifier (predicting the tissue of origin). Supervised machine learning and deep learning models will be developed and integrated using ensemble techniques. The integrated dataset will be divided into training and internal validation sets to optimize model performance and minimize overfitting. Multi-omics data integration will be employed to identify features associated with cancer presence and tissue of origin. These features will be systematically evaluated to assess their compatibility with ctDNA-based assays. Based on this evaluation, ctDNA-compatible signatures will be selected and used for the development of blood-based MCED and MRD assays. The resulting models are intended to support scalable cancer detection and longitudinal disease monitoring.

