### Specimen collection and processing

To minimize batch effects across study cohorts, specimen collection and processing procedures were standardized as much as possible between the MONSTAR-SCREEN-3 study and the ToMMo cohort. For proteomic and metabolomic analyses, blood samples were collected in EDTA-2Na tubes, kept at 4 °C, and centrifuged within 8 h of collection at 2,330 × g for 10 min at 4 °C. The obtained plasma was aliquoted and stored at – 80 °C. For salivary microbiome analysis, saliva samples were collected using Mini centrifuge tubes and stored at – 80 °C immediately after collection. Tumor specimens in the MONSTAR-SCREEN-3 study were collected and stored in accordance with a standardized protocol, ensuring consistency in tissue handling and preservation. WES and WTS analyses of these tumor samples were centrally performed by GxD company, using harmonized pipelines to maintain analytical uniformity. For ctDNA analysis, blood samples were collected using PAXgene Blood ccfDNA tubes. Samples were centrifuged within 7 days after collection: the first centrifugation was performed at 1,900 × g for 15 min at 15–25 °C, followed by a second centrifugation at 1,900 × g for 10 min at 15–25 °C. The separated plasma was stored at − 80 °C until analysis. Although the analytical methods for WGS and fecal microbiome analyses differed between the MONSTAR-SCREEN-3 study and the ToMMo cohort, systematic biases were minimized during AI classifier development by applying standardized feature scaling across datasets.

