### Study period

The enrollment period will extend from February 27, 2024, to September 30, 2026, and the overall study period will continue until March 31, 2027.

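### Control plasma for the new proteome may date from 2013 while case plasma dates from 2024 or later, so storage time can track the cancer label in the proteomic layer

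*Protocol article*

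**What the plan says.** All references are to the protocol article.

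- **Controls.** Eligibility criteria: "Individuals who participated between May 2013 and September 2025" in either ToMMo cohort, subject to consent, no history of malignancy and an age limit.
- **Control proteome.** Development of AI classifiers: "Plasma proteomic analysis will be performed on approximately 1,000 archived plasma samples from the ToMMo biobank using the O-link HT system". This is a new assay on stored material.
- **Cases.** Study design: "MONSTAR-SCREEN-3 (UMIN000053975), launched in 2024". Eligibility criteria: "Participants who, as of March 2026, are enrolled in the MONSTAR-SCREEN-3 study". Study period: "The enrollment period will extend from February 27, 2024, to September 30, 2026".
- **Alignment.** Eligibility criteria: "the age and sex distributions of ToMMo participants will be strictly adjusted to match those of patients with solid tumors", the reference being the preceding MONSTAR-SCREEN-2 study. No other matching variable is named.
- **Handling.** Specimen collection and processing: "To minimize batch effects across study cohorts, specimen collection and processing procedures were standardized as much as possible". For proteomic and metabolomic plasma, the section fixes the tube, holding temperature, time to centrifugation, spin and freezing at −80 °C. It acknowledges differing methods only for WGS and the fecal microbiome, and names feature scaling as the remedy for those.

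No section restricts, matches or checks collection year or storage duration.

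**The concern.** Every case comes from one cohort and every control from the other, so anything that differs between the cohorts can be learned as cancer. Much of that cannot be undone by analysis. Storage time is different because it varies within the controls, so it can be restricted at selection and tested afterwards. The article does neither, and it presents the plasma layers as harmonised.

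If some proteins change during years at −80 °C, a classifier trained on old controls and recent cases can use them as cancer features. The development AUC would then be too high, and storage-sensitive proteins would compete with real markers in feature selection. The planned internal validation gives no warning, because both parts of a split carry the same difference in storage time.

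**Working it through.** The plan states no figure on this point, so there is none to reproduce. The check has three parts.

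**1. Date arithmetic**

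Inputs: control window 1 May 2013 to 30 September 2025 (Eligibility criteria); case window 27 February 2024 (Study period, taken as the earliest case draw) to 31 March 2026 (Eligibility criteria); study end 31 March 2027 (Study period). Days within the stated months are assumed.

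- Control window: 4,535 days, or 12.4 years.
- Part of it before the first case date: 3,954 days, or 10.8 years. 3,954 / 4,535 = 87%.
- Overlap of the two windows: 581 days, about 19 months.
- Longest possible storage at study end: 13.9 years for a control, 3.1 years for a case.

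**2. How well collection date alone predicts the label**

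The distribution of dates within the windows is not given, so uniform dates are assumed and the control window is varied. The AUC is the probability that a random case was collected later than a random control. A control drawn before the first case date always counts as earlier. For a control drawn in the overlap, cases run on for a further 182 days in a 763-day case window, so the probability is 182/763 + (581/763) × 0.5 = 0.62.

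AUC = (share of controls before the first case date) + (remaining share) × 0.62

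| Assumed control draws | Share before first case | AUC of date alone |
|---|---|---|
| 2013 to 2017 | 1.00 | 1.00 |
| May 2013 to Sep 2025 | 0.872 | 0.95 |
| 2020 to Sep 2025 | 0.723 | 0.89 |
| 2022 to Sep 2025 | 0.575 | 0.84 |
| Feb 2024 to Sep 2025 | 0 | 0.62 |
| Both groups Feb 2024 to Sep 2025 | 0 | 0.50 |

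A simulation with 400,000 draws per row gave the same values. The Sample size and power section plans around AUCs of 0.85 and 0.90. The table measures how closely date and label are tied. It does not estimate classifier bias, because collection date is not a listed classifier input.

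**3. What drift could do, as illustration only**

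Suppose k independent proteins each differ by d standard deviations between old and recent plasma, all controls are old, and nothing else differs. Then AUC = Φ(√k · d / √2).

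| | k = 20 | k = 50 | k = 100 |
|---|---|---|---|
| d = 0.2 | 0.74 | 0.84 | 0.92 |
| d = 0.3 | 0.83 | 0.93 | 0.98 |

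Both d and k are assumptions. Independence matters: for shifts in one direction with common correlation ρ, the squared separation becomes k·d² / (1 + (k − 1)ρ). With k = 50 and d = 0.2:

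- ρ = 0.1: 2 / 5.9 = 0.339, AUC = Φ(√0.339 / √2) = 0.66.
- ρ = 0.2: 2 / 10.8 = 0.185, AUC = Φ(√0.185 / √2) = 0.62.

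Shifts of mixed sign could give higher values. A mixture of old and recent controls is outside this formula.

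**Do the stated safeguards catch it?** Feature scaling is named for other layers. Applied to pooled data, it would leave a group offset in place. Applied within each cohort, it would also remove true cancer differences, because cohort and label coincide.

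**The case against.** The strongest reply is that an eligibility window is not a sample-selection rule. Draws from 2024 and 2025 are eligible, access goes through a ToMMo committee, and the choice of aliquots may be set out in a full protocol that is not shown. This stands in part: the actual dates are unknown, and the association may be weaker than the uniform case suggests. It does not remove the point. The article itself states the window, the matching variables and the handling controls, and together these allow storage time to follow the label.

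Three stronger readings that a reader might infer are not supported.

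- **That the performance test will fail because its controls are freshly drawn.** The 200/200 test is a ctDNA analysis on plasma from PAXgene tubes, and a selection step for ctDNA-compatible signatures lies in between. The article gives no direct route from protein drift in EDTA plasma to the sensitivity and specificity of the primary endpoint.
- **That the metabolome is equally affected.** A new assay of archived control plasma is stated for proteomics only. Study design says that development uses existing data, so control metabolomes may have been measured soon after collection. Their storage time at assay is unknown.
- **That the illustrative AUCs measure the bias.** They assume independent proteins and uniformly old controls, and modest correlation lowers them sharply.

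It can also be said that storage age is only one facet of cohort and label being fully aliased. That is true, but it is a facet that can be measured and reduced.

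**Conclusion.** The concern holds for the proteomic layer and the development stage. As written, the selection and alignment rules let storage time track the cancer label. That may inflate the development AUC and the internal-validation results and misdirect feature selection, and an internal split would not reveal it.

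What is firm is the pair of windows: controls may predate the assumed first case draw by up to 10.8 years, with about 19 months of overlap. What is assumed is that case plasma dates from the 2024 launch onward, that 27 February 2024 is its earliest date, and that dates are uniform. The size of the effect on any classifier cannot be derived from the document. The point deserves a change before samples are drawn. It is not evidence that the classifier is already biased.

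**What to change.** 1. In the classifier-development section and the Eligibility criteria, add collection date to the age and sex alignment. Prefer ToMMo plasma collected in 2024 and 2025, and compare it with cases from the same calendar window where feasible. Otherwise use the most recent draws. Restricting the controls alone leaves a date AUC of 0.62 under uniform dates; restricting both groups to the shared window brings it to 0.50.
2. Report collection dates and storage time at assay by group. Include the metabolome, so that its position becomes known.
3. Test each protein against storage time within controls, using a prespecified threshold, and exclude storage-sensitive proteins at least in a sensitivity analysis. Selecting only recent controls removes most of the variation this test needs. It should therefore be run where older controls are used, or in other ToMMo samples with proteomic data spanning several years, if available.
4. Report the classifier score against storage time within controls. A clear trend would be a warning.

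The cost is a selection rule and a screening step that use collection dates a biobank should hold. The downside is a smaller pool for age and sex matching and the possible loss of some real markers. Whether enough recent, suitably aligned samples exist is not stated, hence the fallback to the most recent draws.

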### Clinical performance test of MCED and MRD assays

The clinical performance of MCED and MRD assays will be evaluated using approximately 200 samples, each from the MONSTAR-SCREEN-3 study and the ToMMo cohort. In the MONSTAR-SCREEN-3 study, approximately 200 archived plasma samples collected from participants in the main study will be analyzed for ctDNA. In the ToMMo cohort, up to 200 participants will be newly recruited after obtaining written informed consent. In addition to routine ToMMo blood collection (36 mL), an additional 10 mL of blood will be drawn using a ccfDNA PAXgene tube for ctDNA analysis.

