### Exclusion criteria

Participants who are judged by the investigator to lack sufficient decision-making capacity regarding the conduct of this study will be excluded.

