## Discussion

This study represents the first large-scale, integrative multi-omics analysis for cancer detection in Japan, utilizing two nationwide cohorts, MONSTAR-SCREEN-3 and ToMMo, to develop highly sensitive MCED and MRD assays. By integrating genomic, transcriptomic, proteomic, metabolomic, and microbiome data through AI-driven modeling, the study aims to overcome the sensitivity limitations of conventional single- or dual-omics approaches and to establish an innovative liquid biopsy platform for both early detection and post-treatment monitoring.

Liquid biopsy-based MCED assays, such as Galleri and CancerSEEK, have demonstrated the feasibility of detecting multiple cancer types using cfDNA methylation, fragmentation patterns, copy number alterations, and circulating protein biomarkers [6, 7]. Across major prospective studies, overall sensitivities range from approximately 27% to 72%, while specificity consistently exceeds 98–99%. However, the sensitivity for early-stage cancers remains limited, typically around 30–50%, underscoring the need for next-generation assays with improved detection capability [6–11]. Similarly, MRD assays have shown promise for detecting molecular residual disease following curative therapy. Tumor-naive assays, which do not require prior tumor sequencing, are more broadly applicable in clinical practice but generally demonstrate lower sensitivity compared with tumor-informed approaches, particularly in early-stage and low-shedding tumors [12]. This challenge highlights the need to develop next-generation MRD assays capable of detecting minimal disease burden with higher sensitivity across diverse clinical settings. The present study seeks to address these needs through an AI-driven, multi-omics integration strategy designed to enable comprehensive and highly sensitive detection of both early-stage and residual disease.

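### Controls are labelled cancer-free by past history alone, so an undiagnosed cancer that tests positive counts as a false positive in primary specificity

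*Protocol article*

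**What the plan says.** In the protocol article, Eligibility criteria states that "ToMMo participants must have no history of malignant tumors (4)" and that they "must be between 20 and 75 years of age at the time of consent (5)". The single rule under Exclusion criteria is: "Participants who are judged by the investigator to lack sufficient decision-making capacity regarding the conduct of this study will be excluded". Neither section mentions a cancer work-up, a period of cancer-free follow-up, or a date at which cancer history is judged.

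There are two sets of controls:

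- **Development.** About 1,000 people with existing data and archived plasma, whose cohort participation falls between May 2013 and September 2025 (Eligibility criteria; Development of AI classifiers).
- **Performance test.** "In the ToMMo cohort, up to 200 participants will be newly recruited after obtaining written informed consent" (Clinical performance test of MCED and MRD assays).

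Study period gives the dates: "The enrollment period will extend from February 27, 2024, to September 30, 2026, and the overall study period will continue until March 31, 2027". Endpoints names sensitivity and specificity among the primary measures. For existing multi-cancer tests, the Discussion reports that "specificity consistently exceeds 98–99%" and puts early-stage sensitivity at around 30–50%.

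**The concern.** The label looks backward. A person with a preclinical cancer at the blood draw has no past malignancy and so qualifies as a control, yet preclinical disease is what a multi-cancer early detection test is meant to find. If the assay detects that cancer, the plan as stated scores a correct result as an error. The resulting bias in a primary endpoint runs in one direction only. The confidence interval does not reflect it, and recruiting more controls of the same kind would not reduce it.

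At the specificities quoted for existing tests, 200 controls yield only 2 to 4 false positives (1–2% of 200). One misfiled true detection would be a visible part of that count.

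**Working it through.** The plan states no figure on this point, so there is none to reproduce.

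**Step 1: observation time.**
- New controls: 30 September 2026 to 31 March 2027 is 182 days, or 6.0 months, for the last one enrolled. Those enrolled earlier have longer.
- Archived controls: from the close of the participation window (end of September 2025) to study end is 18 months. From its opening (May 2013) it is about 13.9 years. The six-month limit does not apply to them.

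**Step 2: inputs for the size of the bias.**
- Share p of controls with undiagnosed cancer: not in the document, so assumed. The Introduction gives about one million new cases a year in Japan. Over an assumed 120–125 million people this is 0.80–0.83% per year at all ages. I take 0.4–1% as the working range and show 2% as a stress value, because controls are matched to the age and sex of solid-tumour patients (with a cap at 75).
- Sensitivity Se for such cancers: 30–50%, the early-stage range in the Discussion.
- True specificity Sp: 99% or 98%, from the benchmark in the Discussion.

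**Step 3: formulas.**
- Apparent specificity = (1 − p)·Sp + p·(1 − Se)
- Loss = Sp − apparent specificity = p·(Se − (1 − Sp))
- Share of apparent false positives that are hidden cancers = p·Se / (1 − apparent specificity)

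At p = 0.4%, Se = 30%, Sp = 99%:
- loss = 0.004 × (0.30 − 0.01) = 0.00116, or 0.12 points
- share = 0.0012 / 0.01116 = 11%

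At p = 1%, Se = 50%, Sp = 99%:
- loss = 0.01 × 0.49 = 0.0049, or 0.49 points
- share = 0.005 / 0.0149 = 34%

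| p | Hidden cancers in 200 | Chance of at least one | Hidden and test-positive | Loss in points (Sp 99%) | Share of false positives (Sp 99%) | Same share (Sp 98%) |
|---|---|---|---|---|---|---|
| 0.4% | 0.8 | 55% | 0.24–0.40 | 0.12–0.20 | 11–17% | 6–9% |
| 0.8% | 1.6 | 80% | 0.48–0.80 | 0.23–0.39 | 19–29% | 11–17% |
| 1% | 2.0 | 87% | 0.60–1.00 | 0.29–0.49 | 23–34% | 13–20% |
| 2% | 4.0 | 98% | 1.2–2.0 | 0.58–0.98 | 38–51% | 23–34% |

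The ranges within a row run over Se = 30–50%.

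**Step 4: against sampling error.** The exact (Clopper–Pearson) 95% interval for 198 of 200 is 96.4–99.9%. Its lower limit is 2.6 points below the estimate, well beyond the 0.1–0.5 point bias.

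**Step 5: archived controls.** If history is judged at the draw, the same 0.4–1% would mislabel 4 to 10 of 1,000 training controls. If it is judged at data extraction, cancers recorded by then are already excluded and the number is smaller. The article does not say which applies.

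**The case against.** The strongest reply is that this is a condensed article. The full protocol may fix the date of assessment, the follow-up or a link to cancer records, and silence on those details is not an error. The bias is also small, lies inside the sampling error of 200 controls, and understates specificity in a study that tests no formal hypothesis. All of that stands. What remains is that the article does state the rule that acts as the reference standard for a primary endpoint, and that rule, as worded, looks only backward.

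A reader might infer three stronger things that the document does not support:

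- **That the short observation period contaminates the training data.** The six months concern only the last new performance-test controls. For archived controls mislabelling is possible, but it depends on a date the article does not give.
- **That hidden cancers raise a 98–99% specificity cut-off and so cost early-stage sensitivity.** The plan sets no such cut-off. The 98–99% describes other assays, and classifier precision is planned on the AUC.
- **That the loss reaches about one point or more.** Combining an assumed 1.5% with 72% sensitivity gives 200 × 0.015 × 0.72 = 2.2 people, or 1.1 points. But 72% is the top of the overall sensitivity range, not the early-stage one, and the 1.5% has no source in the document. Nor can cancers diagnosed over several later years be counted as mislabelled, since nothing shows that they were detectable at the draw.

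**Conclusion.** The point holds in a limited form. Primary specificity is measured against absence of a known past cancer, with no stated reference date, and the last new controls can be observed for at most six months. Under an assumed 0.4–1% undiagnosed cancer and 30–50% sensitivity, apparent specificity is understated by about 0.1–0.5 points. That is a quarter of a person to one person in 200. It is conservative and smaller than the sampling error, but would make up roughly 11–34% of apparent false positives at a true specificity of 99% (6–20% at 98%). For the archived training controls, the article neither establishes nor rules out mislabelling.

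The result depends most on the assumed share of undiagnosed cancer, which the document does not give. It is worth correcting because the bias has a known direction, affects a primary endpoint, and can be reduced cheaply if the cohort's records allow.

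**What to change.** 1. **Archived controls.** Judge cancer status at data extraction, and exclude controls with a cancer recorded within a fixed window after the draw. The sponsor should choose the window in advance and select only draws that allow it to be completed.
2. **New controls.** Re-check cancer status in ToMMo records as late as the study period allows. Do this for every control whatever the assay result, because removing only test-positive controls would push specificity upward.
3. **Reporting.** Report specificity as planned, and again without the controls diagnosed by that check. Describe the primary figure as specificity against *no known cancer*.

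**Cost.** A sentence or two in the eligibility and analysis text, and a query on an existing cohort. No new participants or procedures are needed.

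**Downsides.**
- It depends on ToMMo holding later cancer status and being able to release it, which the article does not say.
- Some recent archived draws may be lost.
- Training controls will have had longer follow-up than test controls, and this should be stated when results are read.
- For the last new controls the re-check still falls within six months, so it will catch only part of the hidden cancers.

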**Methods:**

This study leverages clinical information and biospecimens from patients with cancer and cancer-naïve individuals. Samples from patients with cancers will be derived from the MONSTAR-SCREEN-3 study, while those from cancer-naïve individuals will be obtained from the Tohoku Medical Megabank Project. Comprehensive analyses will include whole-genome sequencing (WGS), whole-exome sequencing (WES), whole-transcriptome sequencing (WTS), proteomics, metabolomics, and microbiome profiling using stool and saliva. Artificial intelligence (AI)-based multi-omics integration will be performed to develop novel MCED and MRD assays and to evaluate their clinical performance. The primary endpoints are the sensitivity and specificity of MCED and MRD assays.

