Moreover, unlike conventional screening programs that focus on a small number of cancer types, this study aims to expand detection to approximately 15 malignancies. By aggregating multiple cancers within a single screening framework, MCED increases the effective disease prevalence, which is a critical determinant of positive predictive value in population-based screening [14]. This conceptual advantage is particularly important for cancers with low individual incidence, such as pancreatic cancer, where single-organ screening approaches are inherently limited. To improve clinical interpretability after a positive result, this study incorporates an AI-based Cancer Signal Origin Classifier to estimate the tissue of origin, thereby supporting more targeted diagnostic follow-up. In addition, while most previously reported MCED studies have focused primarily on solid tumors, our study uniquely incorporates hematologic malignancies within the MONSTAR-SCREEN-3 platform. By capturing both solid and hematologic tumors, this project enables the development of a truly pan-cancer detection framework, further expanding the potential clinical impact of MCED and MRD assays. From a population health perspective, MCED and MRD assays represent a promising strategy to address the substantial and growing societal burden of cancer by enabling earlier detection and shifting treatment toward less intensive and more effective interventions. Earlier diagnosis has the potential not only to improve clinical outcomes, but also to reduce downstream medical costs associated with advanced-stage disease, long-term care, and productivity loss. To ensure sustainable implementation at the population level, however, cost considerations, including potential financial burden for individuals and healthcare systems, should be carefully addressed. This expanded scope has the potential to substantially enhance the clinical utility of MCED and MRD testing, contributing to earlier detection and improved outcomes across a wider range of cancers.

Ultimately, this study is expected to lay the foundation for next-generation liquid biopsy diagnostics that are both highly sensitive and broadly applicable across cancer types. By integrating multi-layered omics data with harmonized protocols and advanced AI analytics, this approach could not only improve early detection and recurrence monitoring, but also guide risk-adapted surveillance and therapeutic decision-making in clinical practice.

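### Controls are adjusted to another study's solid-tumour patients and capped at age 75, so they are not matched to the MONSTAR-SCREEN-3 cases and age can partly discriminate the two groups

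*Protocol article*

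**What the plan says.** **Cases.** The Abstract (Methods) states: "Samples from patients with cancers will be derived from the MONSTAR-SCREEN-3 study". The only age rule for them, under Eligibility criteria, is a lower bound: "Participants in the MONSTAR-SCREEN-3 study must be 18 years of age or older". Haematologic cancers are included by intent; the Discussion says "our study uniquely incorporates hematologic malignancies within the MONSTAR-SCREEN-3 platform".

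**Controls.** ToMMo participants have no history of malignancy and "must be between 20 and 75 years of age at the time of consent". To secure comparability, their age and sex distributions "will be strictly adjusted to match those of patients with solid tumors enrolled in the previous MONSTAR-SCREEN-2 study".

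**Claimed comparability.** The section on developing the AI classifiers describes the development set as "approximately 1,000 consecutive cancer patients (MONSTAR-SCREEN-3) and 1,000 background-aligned cancer-naïve individuals (ToMMo", and then calls the same controls background-matched.

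**Use.** About 1,000 cases and 1,000 controls serve classifier development. About 200 cases and up to 200 controls serve the clinical performance test. The primary endpoint is assay performance, including sensitivity and specificity. The Statistical analysis section gives these with 95% confidence intervals, plus AUC for the classifiers.

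**The concern.** The matching target is not the comparison group. Controls are shaped to solid-tumour patients of an earlier study, whereas the cases come from a later study with a different case mix that includes a disease class absent from the target. The development cases are also taken consecutively, so they are not selected on age. Under the cap, no control over 75 at consent is eligible for comparison with a case over 75.

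By requiring strict adjustment for age and sex, the article itself treats them as confounders. If they remain unbalanced, a feature that tracks age can be rewarded as a cancer signal. The article's own safeguards would not show this. An internal validation split inherits the age structure of the data it is split from, and the 200/200 set falls under the same eligibility rules. The feature scaling under Specimen collection and processing is aimed at differences in analytical method, not in age. The estimates at stake are the primary sensitivity and specificity and the classifier AUC.

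**Working it through.** **1. What is fixed by the text**

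| | Cases | Controls |
|---|---|---|
| Source | MONSTAR-SCREEN-3 | ToMMo |
| Age | 18 or older, no upper limit stated | 20–75 at consent |
| Age–sex target | none | solid-tumour patients of MONSTAR-SCREEN-2 |
| Haematologic cancers | included | not in the target |

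The article restricts cases to the control age range nowhere, and nowhere ties controls to the actual cases. It gives no age distribution for either MONSTAR study or for the controls, so there is no figure of its own to reproduce. Everything below rests on assumed ages.

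**2. Over-75 gap, controls following the case distribution truncated at 75**

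Let p be the share of cases over 75. Each such case is older than every control. The other cases have the same ages as the controls. Then

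AUC (age only) = p × 1 + (1 − p) × 0.5 = 0.5 + p/2,

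and the rule *age over 75* has sensitivity p at specificity 1.

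| Assumed p | Age-only AUC | Cases over 75, of 1,000 | of 200 |
|---|---|---|---|
| 5% | 0.525 | 50 | 10 |
| 10% | 0.55 | 100 | 20 |
| 20% | 0.60 | 200 | 40 |
| 30% | 0.65 | 300 | 60 |

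Numerical check with normal case ages: mean 60, SD 12 (10.6% over 75) gives 0.553; mean 65, SD 12 (20.2%) gives 0.601; mean 70, SD 10 (30.8%) gives 0.654.

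**3. The same gap, with the over-75 share filled by the oldest eligible controls**

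If the adjustment replaces the missing over-75s with controls aged 70–75 (an assumption), the age-only AUC falls:

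| Assumed case age | Truncated controls | Filled from ages 70–75 |
|---|---|---|
| mean 60, SD 12 | 0.55 | 0.51 |
| mean 66, SD 11 | 0.60 | 0.54 |
| mean 70, SD 10 | 0.65 | 0.58 |

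The AUC is therefore sensitive to how the control sample is filled. The lack of controls over 75 is not.

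**4. Wrong reference study**

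Ignoring the cap, if cases are on average d years older than the reference population (common SD 12), AUC = Φ(d / (12√2)): 0.547, 0.593 and 0.638 for d = 2, 4 and 6. With the cap and case ages of mean 66, SD 11, a reference population 4 years younger raises the age-only AUC from 0.60 to 0.67, and one 4 years older lowers it to 0.55. The direction cannot be known from the article.

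**5. From age-only figures to spurious sensitivity**

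The value p is an upper bound. Only over-75 cases that the assay would otherwise miss can be gained, so the gain is at most p × (1 − true sensitivity at that age). With p = 20% and a true sensitivity of 50%, that is 0.20 × 0.50 = 10 percentage points.

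**6. After repair**

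With controls carrying the age distribution of the actual cases over a common range, p = 0 and the age-only AUC is 0.50.

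**The case against.** A reader might infer that age alone separates cases from controls. The documents do not support that. The age ranges overlap from 20 to 75, and even the illustrative AUCs of 0.55 to 0.65 describe partial discrimination.

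Further points against a strong reading, all of which stand:

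- The share of cases over 75 is unknown, and 0.5 + p/2 holds for only one way of filling the control sample.
- The difference between the two MONSTAR studies need not add to the over-75 gap; it could offset part of it.
- Age and sex are retrieved as clinical information but not named as classifier inputs, and the final assays use selected signatures compatible with ctDNA. The bias realised depends on how closely those signatures track age.
- The cap applies at consent. The text does not say which consent counts, and ToMMo participation dates from May 2013. If cohort consent counts, some newly bled controls could be over 75 at the draw.
- An earlier study is an understandable planning proxy.

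These points limit the size and certainty of the bias. They do not restore the claimed comparability: the target population is still a different one, it still omits haematologic patients, and nothing else in the article corrects for that. If MONSTAR-SCREEN-2 itself had patients over 75, strict adjustment to it under the cap is not achievable either.

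**Conclusion.** The concern holds as a defect in the stated matching rule. The controls are not matched to the cases they are compared with, and under the cap specificity above about age 75 is essentially not estimated, while cases of that age enter sensitivity. Age can partly discriminate the groups, so AUC, sensitivity and specificity may be biased: probably upward through the over-75 gap, and in an unknown direction through the choice of reference study.

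The design facts are certain; the size is not. For an assumed 10–30% of cases over 75, the age-only AUC is 0.55–0.65 with truncated controls and smaller if the oldest eligible controls fill the gap. These figures show what a classifier could exploit. They do not estimate the bias that will occur.

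**What to change.** 1. In Eligibility criteria, change the matching target to the age–sex distribution of the MONSTAR-SCREEN-3 patients actually analysed, haematologic cases included. Do this separately for the 1,000/1,000 and the 200/200 sets.
2. If controls are already selected, weight them to that distribution within the overlapping age range.
3. Report AUC, sensitivity and specificity in the common age range alongside the overall result. Report cases over 75 separately, as sensitivity only.
4. Give the AUC of a model with age and sex only, as the benchmark for the classifiers.

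**Cost.** A wording change and some extra analysis. The common-range estimate loses precision because cases over 75 drop out of it: at an assumed 20%, 160 of 200 performance cases remain (200 − 40). That is a reason to report it beside the overall result and not in its place. Re-targeting looks feasible: case eligibility is set as of March 2026, enrolment runs to 30 September 2026, and ToMMo has about 150,000 participants. The article does not say how many of them are cancer-naïve with suitable stored samples and omics data, so this needs confirming.
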